**Figure 1 F1:**
[figure not shown]
**Overview of the design of the RCT**.

## Discussion

In the present study consensus was reached by low vision therapists, clinical physicists and researchers in the field of low vision on a standard protocol for training in the use of CCTVs. The protocol consists of various chapters including several exercises within each chapter. The focus of the training protocol is on ergonomics, basic operation skills, reading, writing, looking at pictures and photographs, and carrying out hobbies. An RCT was conducted to test the effectiveness of the protocol by comparing an intervention group, i.e. patients who receive both instructions provided by the supplier and the new standard training, with a control group, i.e. patients who receive only the instructions from the supplier.

The study will concentrate on predictors of training effects. For example, there might be a 'dose-response' relation between the number of sessions or the time per session and the effect of treatment in terms of primary [15-17] and secondary outcomes. Moreover, we expect that low vision specialists will be able to use our results in deciding which patients will be eligible for training in the future, for example patients with a certain visual acuity or patients who suffer from non-visual co-morbid conditions. Finally, optometrists may have a better indication for referring patients to MRCs for additional training. Moreover, by studying patient files and obtaining data from the participants during the home visits, this study will provide knowledge about the process of counseling and prescribing CCTVs to visually impaired adults (e.g. knowledge about which patients were prescribed a CCTV and about their rehabilitation needs). Consequently, the process of delivering CCTVs will become more transparent. At the time the study was conducted, the exact content of the instructions suppliers provide when they deliver CCTVs to patients' homes was unknown, as well as the time taken for these instructions. We decided not to inform suppliers about the study, to avoid them starting to over perform on their usual instructions, which may vary somewhere between no instructions to basic instructions on how to operate the CCTV. If they would have been informed, a smaller effect of the new standard protocol for CCTV training may be expected. Also, we did not know in advance which supplier would be involved in delivering a CCTV to a particular eligible patient. This depends on the insurance company of the patient and the rehabilitation center that has CCTVs of specific providers on display. In the course of the present study information about these instructions was obtained from participants. Comparability between the treatment and control group with regard to the instructions of the suppliers will be investigated.

There are some limitations to the present study. First, the recruitment of participants by the MRCs took longer than expected. Reasons for this delay were: lack of eligible patients, lack of interest of clients, workload of low vision specialists who were required to invite eligible participants and ethical considerations of a low vision specialist who had conscientious objections to inviting participants with a need for CCTV training. This low vision specialist only invited patients who needed a CCTV, but who could manage without training, so that it would not matter if a patient would be randomized into the control group. Although several actions had been undertaken to convince the low vision specialist of the purpose of the study, and that all eligible patients with a CCTV indication should be invited, it did not work out properly. For this particular MRC, this has caused a selection bias which may lead to an underestimation of the treatment effect which influences generalizability of the results. Therefore, data will be analyzed with and without patients from this specific site.

Second, we only focused on CCTVs with stand mounted cameras and/or displays, since these are the types that are most commonly prescribed in the Netherlands. In addition to stand mounted CCTVs, there are 'mouse' style CCTVs and CCTVs with handheld or head-mounted cameras. All of these devices are more portable than stand mounted CCTVs. However, battery power options tend to be heavy and expensive and, mouse style CCTVs especially, have a limited range of magnification[22]. Head-mounted CCTVs can be used for a wide variety of tasks, nevertheless, patients with macular disease showed better functioning using optical aids compared to head-mounted CCTVs for the majority of tasks in research by Culham et al.[38].

Third, for scientific reasons it would have been preferable to standardize the training protocol further. For instance, to standardize the frequency and the total minutes of training each participant receives, as well as the amount of time practicing with each assignment. However, in daily practice it is very important to amplify care to the characteristics of the individual patient (e.g. learning abilities, endurance and limitations due to co-morbidity). For this reason, training was adjusted to the rehabilitation needs of the participants as well as to their learning style and learning rate, e.g. when participants had major problems with reading, the reading assignments were practiced more intensely. Another advantage of this method is that when the training program has been proven effective, only a few adjustments might be necessary before implementing the protocol in daily practice.

Finally, it would have been preferable to offer placebo-training to the control group, to rule out a Hawthorne effect. An attention deficit in this group may result in a poorer outcome, e.g. a lower experienced quality of life. However, the study of Reeves et al. did not show significant differences in task performance and quality of life between patients who received conventional low vision rehabilitation enhanced by home visits from a rehabilitation officer (who gave advice and demonstrations on the use of LVAs, supplied alternative LVAs and provided patient support) or from a community care worker (who did service as a control for the contact time with patients)[39].

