#### Final content of the CCTV training protocol

In designing the final content of the training protocol, the age of the actual users of CCTVs was taken into account. In the Netherlands the majority of CCTV users is estimated to be above the age of 70 years. Many older visually impaired patients cannot concentrate for long periods. Therefore, based on the experience of the low vision therapists, two 30 minute sessions separated by a break of 15 to 30 minutes were scheduled. The frequency of training was once a week. The amount of training depended on the learning strategies of the individual patients. Patients were trained until they had practiced with every assignment or until no further improvement could be reached.

Table 1 summarizes the main components of the CCTV training protocol. The protocol focused on various aspects, similar to those in previous studies such as: ergonomics, basic instructions for operating the CCTV and tracking skills with the X-Y table [6,15-19,24]. When participants were familiar with the basic aspects of the CCTV, reading was practiced with different reading materials. Furthermore, looking at pictures and photographs was practiced, since this demands some special skills (e.g. with respect to preventing glare). Next, participants practiced writing with their CCTV, using different exercises. Finally, participants were asked which hobbies they would like to practice and some examples were given. Throughout the training program, participants practiced with the easier assignments before they tried the more difficult ones (easy-to-difficult strategy[17]). Hands on training was given [17], with direct feedback to the participants, to avoid the adoption of incorrect habits. Training was given by low vision therapists from the three organizations, who scored the patient's progression by registering all the assignments patients could carry out and also which particular assignments patients found difficult.

**Table 1 T1:** Main components of the standard training protocol in the use of CCTVs.

Components	Details	
Elements - Ergonomics	- Position of CCTV in the room - Posture for working with CCTV - Height of CCTV and working distance	
Elements - Basic operation instructions	- On/off switch - Magnification - Image contrast - Position of lights and camera - X-Y table and basic tracking skills	

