Elements - Reading (different materials)	- Basic reading assignments (e.g. reading words/small sentences) - Newspapers, books, magazines, postcards, medicine bottles etc.	
Elements - Watching pictures	- Pictures and photographs with different pixel amounts	
Elements - Writing (different materials)	- Basic writing assignments (e.g. drawing crosses in boxes) - Virgin and zoned paper, cheques, forms	
Elements - Hobbies and other CCTV skills	- Interests and hobbies of the patients are discussed and practiced (e.g. painting, fiddling, sewing, drawing etc.)	
Applied techniques	- Hands on training - Easy-to-difficult strategy	
Number of sessions	- Variable, adjusted to the individual patients need	
Frequency	- Once a week	
Duration	- Sixty minutes per session	
Format	- Face-to-face	
Location	- Patients' home environment	

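### The dose-response aim relates benefit to number of sessions, but sessions were set by the patient's own need and progress, so the slope is confounded in an unknown direction

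*Protocol article*

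**What the plan says.** The Discussion of the protocol article states an aim: "The study will concentrate on predictors of training effects". Its first example is a possible dose-response "relation between the number of sessions or the time per session and the effect of treatment", for both primary and secondary outcomes. The same paragraph expects that "low vision specialists will be able to use our results in deciding which patients will be eligible for training in the future", and mentions visual acuity and non-visual co-morbidity as possible criteria.

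The section on the final content of the training protocol explains how the amount of training came about: "The amount of training depended on the learning strategies of the individual patients". It then gives the stopping rule: "Patients were trained until they had practiced with every assignment or until no further improvement could be reached". Table 1 lists the number of sessions as variable and fitted to need, and the duration as "Sixty minutes per session". The third limitation in the Discussion adds that training followed learning style and learning rate, and that "when participants had major problems with reading, the reading assignments were practiced more intensely".

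The Statistical analysis section adjusts for relevant confounders and names age, visual acuity and any baseline imbalance. It does not mention learning rate or progress during training.

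**The concern.** A dose-response relation can be read as an effect of dose only if patients with different doses are otherwise comparable. Here the dose is decided during treatment, by the patient's ability and by how training is going. One of the two stopping conditions is the response itself. The same trait, how readily a patient learns to use the device, therefore influences both the number of sessions and the gain in reading.

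At stake is a secondary conclusion with practical reach. If the training is adopted as the national instruction, as the Background foresees, a published slope of benefit on sessions could be taken as guidance on how much training to give. The slope could be wrong in size and possibly in sign.

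**Working it through.** **1. The passages side by side.** The aim needs sessions to vary independently of response. The stopping rule has two branches, and they work in opposite directions:
- Training ends when every assignment has been practised. A slow learner plausibly needs more sessions to get there, so high session counts go with low ability and the slope is pulled downward.
- Training ends when progress stops. A poor responder may reach that point early, so low session counts go with poor response and the slope is pushed upward.

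The article does not say how many patients ended by each route. More intense practice of reading assignments for those with major reading problems shows that training depended on difficulty, but intensity is not a count of sessions.

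**2. Who contributes.** Controls received no training before follow-up, so session number varies only in the trained arm. The sample size gives the number of evaluable patients. With a difference of 20 wpm, SD 33.5, two-sided alpha 0.05 and power 0.85:

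n = 2 × (1.960 + 1.036)² × 33.5² / 20² = 50.4, so 51 per arm; 51 / 0.83 = 61.4, so 62.

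This reproduces the stated 62 (two-sidedness is assumed; the article does not state it). After 17% loss, 62 × 0.83 = 51.5 trained patients remain.

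**3. Illustration of the bias.** The article gives no input for this, so every value here is assumed. Let L be learning rate in SD units and S sessions, averaging 6, rounded to whole sessions. S changes by a sessions per unit of L, with other variation of SD 1. Gain is 2 × S + g × L plus noise of SD 20 wpm. The true slope is +2 wpm per session. The expected fitted slope is

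2 ± g × a / (a² + 1 + 1/12),

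where 1/12 is the rounding variance. The sign is minus if slow learners get more sessions and plus if poor learners stop early. For a = 1 and g = 10: 10 / 2.083 = 4.8, giving -2.8 or +6.8.

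| a | g | slow learners get more | poor learners stop early |
|---|---|---|---|
| 0.5 | 5 | +0.1 | +3.9 |
| 1 | 5 | -0.4 | +4.4 |
| 1.5 | 5 | -0.3 | +4.3 |
| 0.5 | 10 | -1.8 | +5.8 |
| 1 | 10 | -2.8 | +6.8 |
| 1.5 | 10 | -2.5 | +6.5 |

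Simulation of 1,000 trials of 51 trained patients per setting agreed closely (for example -2.78 and +6.73 at a = 1, g = 10). If slow learners get more sessions, the slope was negative in 47% to 55% of trials at g = 5 and in 73% to 94% at g = 10. Without confounding (a = 0 or g = 0) it averaged about +2 and was negative in 10% to 27% of trials from noise alone.

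**4. Does the planned adjustment help?** Age, visual acuity and baseline differences can remove only the part of L they predict. They cannot remove dependence on progress seen during training, because that arises after baseline.

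**5. Time per session.** Two half-hour blocks make the scheduled sixty minutes. Variation around a fixed schedule would be departures from it. The Discussion names endurance and co-morbidity as reasons for tailoring training, and these plausibly also affect reading gain.

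**6. Precision for predictors of benefit.** With a 50/50 subgroup split, an arm-by-subgroup interaction has twice the standard error of the main effect. The interaction detectable with 85% power is 2 × 2.996 × SD × √(2/51.46), which is 39.6 wpm at SD 33.5 and 44.8 at SD 37.9 without baseline adjustment. The pre-post correlation r is not given. Assuming r of 0.5 to 0.8 and multiplying by √(1 - r²) gives about 24 to 39 wpm. The design difference is 20 wpm, and the gain in the source study was 89.2 - 71.8 = 17.4 wpm. A continuous covariate would be expressed on another scale.

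**The case against.** The strongest reply is that the relation is worded tentatively, as an example in the Discussion. The Statistical analysis section contains no dose-response model, and a plan not shown may label the analysis exploratory and extend the open list of confounders. The article also admits that the amount of training was not standardised.

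Part of this stands. No model or causal claim is written down. But the aim is stated without hedging, and its first example conflicts with the article's own dosing rule. That is a clash between two stated elements, not missing detail. The admitted limitation concerns comparability and implementation; it is not linked to the dose-response relation.

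Three stronger readings are tempting and are not supported:
- A reader might infer that slow learners certainly received more sessions, so that the slope will be too low or reversed. The second stopping branch can act the other way.
- A reader might infer that predictors will be sought only among trained patients and would show prognosis, not benefit. The article does not say so, and nothing in it excludes interactions using both arms.
- A reader might infer that the results will determine who gets training. The text only expects specialists to be able to use them.

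**Conclusion.** The point holds as a limit on what a dose-response result can mean. Session number depends on ability and on response during training, so a slope of gain on sessions among trained patients is confounded, and the named baseline covariates do not cure it. The direction is open. The size cannot be estimated from the article: the range of about -2.8 to +6.8 around a true +2 wpm per session rests wholly on assumed inputs and shows only that bias of either sign can exceed the effect. Time per session is no better as a dose variable. The primary intention-to-treat comparison is not affected. The change should be made, because it alters what may be concluded and costs little.

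**What to change.** In the Discussion, replace the dose-response aim with a description of the sessions delivered and the reason training ended (all assignments practised, or progress stopped). If an association with sessions or time is still reported, label it exploratory and non-causal and state that sessions depended on progress.

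Examine predictors of benefit, such as visual acuity and co-morbidity, as interactions between arm and pre-randomisation covariates using both arms, reported as exploratory with confidence intervals. Make any use for selecting patients conditional on confirmation, since the intervals will probably be wide.

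The cost is a change of wording and of a secondary analysis, plus recording why training ended if the therapists' progress records do not already show it. What is given up is a causal dose claim that the design cannot support.

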## Conclusion

We believe that the limitations of the study can be considered small compared to the information the study will provide: a new standard training protocol was developed to instruct visually impaired adults in the use of CCTVs. In addition, the effectiveness will be tested in an RCT, which allows us to provide an evidence-based training.

## Abbreviations

AVL: Adaptation to age-related Vision Loss scale; CES-D: Center for Epidemiological Studies Depression scale; CCTV: Closed-Circuit Televisions; LVA: Low Vision Aid; LVQOL: Low Vision Quality Of Life questionnaire; MRC: Multidisciplinary Rehabilitation Center; RCT: Randomized Controlled Trial.
